## **Dose Escalation Rules**

To minimize the risk of this combination to patients, dosing in the first dose level cohort only will proceed by evaluating safety in the first patient for 12 weeks after the dose of CP-675,206. Prior CP-675,206 single-agent data on safety findings from Pfizer studies indicate that a 6-week follow-up interval was appropriate. However, in order to monitor for potential late-onset toxicities due to the combination of CP-675,206 with radiation, this protocol will follow patients for 12 weeks.

Dosing will be conducted in subsequent dose level cohorts of at least 3 patients, with patients assigned to a dose group after verification by the Investigator of eligibility.

Safety considerations in a current dose level will be assessed as follows to determine dose level escalation:

**1.** If no patient experiences a DLT in the first 12 weeks, the trial will proceed to the next dose level cohort

**2.** If 1/3 patients experiences a DLT in the first 12 weeks, expand cohort to 3 additional patients, and then determine:

- 1. • If 1/6 patients experiences a DLT in the first 12 weeks, escalate to the next dose level.
  2. • If ≥2/6 patients experience a DLT in the first 12 weeks, the current dose level will be considered above the maximum tolerated dose and dose escalation will be discontinued.

**3.** If ≥2/3 patients experience a DLT in the first 12 weeks, the current dose level will be considered above the MTD and the preceding dose level cohort will be expanded to a minimum of 6 patients.

The dose escalation will end after DLT is observed in ≥2 out of 3-6 patients treated at any dose level or after 6 patients at the highest dose level defined (CP-675,206, 15 mg/kg) have completed the 12-week observation period.

Additional patients may be entered as needed at any dose level, including intermediate dose levels, to more fully elucidate the pattern of toxicity and/or better define the MTD.

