## **4.4. Dose Limiting Toxicities**

Adverse events and other symptoms will be graded according to the NCI Common Terminology Criteria for Adverse Events version 3.0. (<http://ctep.cancer.gov/reporting/ctc.html>).

Dose-limiting toxicity (DLT) is defined as any of the following when considered related to CP-675,206 therapy:

1. • Any CTC Grade 4 treatment related toxicity of any duration.
2. • Other Grade 3 or greater toxicities that do not recover to ≤ Grade 1 or baseline within 7 days of maximal management
3. • Grade 2 or greater treatment related clinical autoimmune toxicity of critical organs, which are defined as lung, heart, kidney, bowel, bone marrow and nervous system, including the eye (except anterior uveitis).

Assessment of DLTs during the first 12 weeks after CP-675,206 dosing will be completed to determine the next dose level.

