## **Maximum Tolerated Dose**

The MTD will be the maximum dose level of CP-675,206 administered (3, 6, 10 or 15 mg/kg) in combination with radiation, at which no subject experiences a life-threatening adverse event and at which 0/6 or 1/6 patients (<33%) experiences a DLT during the first 12 weeks following CP-675,206 dose administration.

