### **6.1.4. Management of CP-675,206 Toxicity**

CP-675,206 is an immune modulator, so Investigators should be alert for the development of immune-mediated side effects.

The majority of the adverse events reported in early phase trials have been manageable and well tolerated. The most common treatment-emergent, treatment-related adverse event is diarrhea. Diarrhea typically developed 1 to 2 months after the first dose of CP-675,206 (range: 4-72 days).

Although CP-675,206 is a fully human monoclonal antibody, immunogenicity remains a possibility, and thus acute hypersensitivity reactions such as urticaria, pruritus, laryngeal edema, angioedema, bronchospasm, respiratory distress, nausea, vomiting, abdominal cramps and pain, acute back pain, fever, diarrhea, hypotension and fatal anaphylactic shock, as well as sub acute reactions, are also possible. Possible immune-mediated disorders observed involve the skin (vitiligo and cutaneous leukocytoclastic vasculitis), the thyroid gland (autoimmune thyroiditis), the liver (autoimmune hepatitis), the pituitary (hypophysitis) and bone marrow (immune thrombocytopenic purpura). Abnormal lab results that may be immune-mediated include elevations of serum lipase and amylase and liver function tests. There has been one report of treatment-related uveitis, which resolved within 48 hours after treatment with topical steroids. Across all studies, toxicities generally recovered within 12 weeks, allowing continuation of treatment.

If a patient has an adverse event that is thought to be potentially immune-mediated (other than vitiligo), the Investigator should send a blood sample for autoimmune antibody testing.

CP-675,206 is a monoclonal antibody of the IgG2 type, and it is expected that it would cross the placenta if administered to a pregnant woman and could be secreted in breast milk of a lactating woman. The effect of exposure of a fetus or newborn to CP-675,206 is unknown. Women of childbearing potential must agree to use contraception during this trial and for 12 months after the last dose of CP-675,206.

*Note:* In general, it is not expected that the combination of CP-675,206 with this radiation dose will increase CP-675,206-related toxicities. However, radiation of the sites that are the most common autoimmune targets following CP-675,206 administration will be avoided when possible.

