**Table 2. On-trial assessments**

**Test/Assessment: Study Day Number:**

|  | D1 | D2 | D3 | D4 | D5 | D8  (1w) | D15  (2w) | D22  (3w) | D29  (4w) | D43  (6w) | D57 (8w) | D71  (10w) | D85  (12w) |
| --- | --- | --- | --- | --- | --- | --- | --- | --- | --- | --- | --- | --- | --- |
| Weight |  |  | X |  |  | X | X | X | X | X | X | X | X |
| Physical Exam, including signs of autoimmunity |  |  | X1 |  |  | X | X | X | X | X | X | X | X |
| ECOG status |  |  | X1 |  |  | X | X | X | X | X | X | X | X |
| Hematology2,3,4 | X |  |  |  |  | X | X | X | X | X | X | X | X |
| Serum Chemistry3,4,5 | X |  |  |  |  | X | X | X | X | X | X | X | X |
| Microscopic or Dipstick Urinalysis3,4,6 | X |  |  |  |  | X | X | X | X | X | X | X | X |
| Thyroid Function3,4,7 |  |  |  |  |  |  |  |  | X |  |  |  | X |
| Autoantibody Panel3,4,8 | X |  |  |  |  |  |  |  | X |  |  |  | X |
| Human anti-human antibody (HAHA)9 | X |  |  |  |  |  |  |  | X |  |  |  | X |
| Radiation10 | X | X | X | X | X |  |  |  |  |  |  |  |  |
| CP-675,206 Administration |  |  | X |  |  |  |  |  |  |  |  |  |  |
| Immune Monitoring11 | X |  |  |  |  | X | X |  | X |  | X |  | X |
| Blood specimen for genomic analysis12 | X |  |  |  |  |  |  |  |  |  |  |  |  |
| AE Monitoring13 | X | X | X | X | X | X | X | X | X | X | X | X | X |
| Tumor Imaging (CT, MRI)14 |  |  |  |  |  |  |  |  |  |  | X |  |  |

**1.** Tests performed/specimens drawn prior to dosing with CP-675,206.

**2.** Hemoglobin, WBC with 5-part differential (percent and absolute values), platelet count

**3.** Clinically significant abnormalities should be reported as Adverse Events in the CRF.

**4.** Assessments may be performed within 24 hours of the designated timepoints.

**5.** Calcium, chloride, total protein, potassium, random glucose, sodium, blood urea nitrogen/BUN, creatinine, AST/SGOT, ALT/SGPT, alkaline phosphatase/ALP, lactic acid dehydrogenase/LDH, amylase, lipase, albumin, total bilirubin

**6.** Complete urinalysis (with microscopic analysis of centrifuged sediment for casts or other abnormalities); performed at baseline. In subsequent evaluations, dipstick urine testing is allowed in lieu of microscopic analysis, however, microscopic analysis must be performed if dipstick results are abnormal.

**7.** Thyroid stimulating hormone (TSH), T3, T4. Thyroid function tests are also done as part of the pre-trial assessments (within 14 days before treatment begins).

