## **Reporting requirements**

Within one (1) working day, report by **telephone** to the Principal Investigator or research nurse serious adverse events as defined below.These events should also be reported within three (3) working days, in **writing**, to the Principal Investigator. An appropriate adverse event form should be used.

*Associated with the use of the drug/biologic*: There is a reasonable possibility that the experience may have been caused by the drug/biologic.

*Life threatening adverse drug/biologic experience*: Any adverse drug/biologic experience that places the subject, in the view of the investigator, at immediate risk of death from the reaction as it occurred.

*Serious adverse drug/biologic experience*: Any adverse drug/biologic experience occurring at any dose that results in any of the following outcomes:

- Death (including all deaths within 30 days of the last administration of study drug/biologic.

- A life-threatening adverse drug/biologic experience

- Inpatient hospitalization or prolongation of existing hospitalization

- A persistent or significant disability/incapacity

- A congenital anomaly/birth defect

- Any other medical event that, in appropriate medical judgment, may require medical or surgical intervention to prevent one of the outcomes listed above.

*Unexpected adverse drug/biologic experience*: Any adverse drug/biologic experience, the specificity or severity of which is not consistent with the product monograph, or not consistent with the risk information described above as a protocol-specific expected adverse event (see “Expected Adverse Events and Protocol-Specific Expedited Adverse Event Reporting Exclusions”, above).

Qualifying serious adverse events must be reported to the UHN Research Ethics Board (REB) according to the UHN REB’s required timeframe.

The Sponsor (IND/CTA holder) will be responsible for reporting all adverse events to the appropriate regulatory agencies (e.g. REB/Health Canada as applicable) as per each agencies individual reporting requirements and within each agencies required timeframe.

Data on all adverse experiences/toxicities (excluding fever and hematologic toxicities), regardless of seriousness must be collected for documentation purposes only. AEs should be followed for 6 weeks after the last dosing of study drug/biologic.

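### The reporting section follows adverse events for 6 weeks, which contradicts the protocol's own 12-week DLT window, its visit schedule and its follow-up of related events to resolution

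*Protocol*

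**What the plan says.** Protocol section 9.2 (Reporting requirements) closes its paragraph on routine AE data with "AEs should be followed for 6 weeks after the last dosing of study drug/biologic".

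The other places that bear on the period are these:

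- **Section 4.2 (Dose Escalation Rules)** first states "Prior CP-675,206 single-agent data on safety findings from Pfizer studies indicate that a 6-week follow-up interval was appropriate". It then departs from that interval: "in order to monitor for potential late-onset toxicities due to the combination of CP-675,206 with radiation, this protocol will follow patients for 12 weeks".
- **Section 4.4 (Dose Limiting Toxicities):** "Assessment of DLTs during the first 12 weeks after CP-675,206 dosing will be completed to determine the next dose level".
- **Section 4.5 (Maximum Tolerated Dose)** requires that "0/6 or 1/6 patients (<33%) experiences a DLT during the first 12 weeks following CP-675,206 dose administration".
- **Sections 4.3 and 6.1.1** hold the escalation decision until the cohort has completed 12 weeks of observation.
- **Table 2 (section 7.2, repeated in section 13)** marks AE monitoring at every visit from D1 to D85. Its note 13 makes AE assessment continuous, and follows related events to baseline, Grade 1 or a judgment of irreversibility.
- **Section 7.3.1** follows related events to resolution or irreversibility and sets no 6-week limit.
- **Section 6.1.4**, on the most common related event: "Diarrhea typically developed 1 to 2 months after the first dose of CP-675,206 (range: 4-72 days").

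**The concern.** Toxicity is the primary endpoint, and the count of DLTs decides whether the next cohort receives a higher dose. The period over which adverse events are recorded should therefore be at least as long as the period over which DLTs are counted. Section 9.2 gives half of it, and the figure it gives is the one that section 4.2 considers and sets aside.

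The section on adverse event reporting is a natural place for study staff to look up the collection period. If they take 6 weeks from it, an event that begins later could be recorded incompletely or not at all. One that begins shortly before week 6 could be dropped before its course is known. The second case matters because one DLT criterion depends on whether a Grade 3 or higher toxicity recovers within 7 days of maximal management. Bowel is also one of the critical organs in the autoimmune DLT criterion, so late diarrhea or colitis bears directly on escalation. The error runs one way: unrecorded DLTs can only make a dose level look safer than it is.

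**Working it through.** **1. The two periods on the study calendar.** CP-675,206 is given on D3. Six weeks is 6 × 7 = 42 days, ending on D3 + 42 = D45. Twelve weeks is 84 days, ending on D87. So 42/84 = one half of the DLT window lies beyond the period in 9.2. The Table 2 visits on D57, D71 and D85 (54, 68 and 82 days after dosing) all fall after D45, and AE monitoring is marked at each.

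**2. Can a reading of 9.2 remove the conflict?** *Followed* has two plausible meanings.

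- If it means how long new events are collected, 9.2 conflicts with the 12-week DLT assessment (4.2 to 4.5, 6.1.1), with AE monitoring to D85 and with continuous assessment (Table 2, note 13).
- If it means how long a known event is tracked, 9.2 conflicts with note 13 and section 7.3.1, which follow related events to an outcome rather than to a date.

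Neither reading reconciles the text.

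**3. Does the stated onset range reach past week 6?** Yes. The upper end, day 72, is 72 − 42 = 30 days beyond it. The protocol does not give the share of onsets after day 42. Assuming uniform onset:

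- over days 4 to 72, the late share is (72 − 42)/(72 − 4) = 30/68 = 0.44;
- over days 30 to 60 (1 to 2 months), it is (60 − 42)/30 = 0.60.

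**4. The protocol's own escalation figures.** Section 10.3 assumes escalation on 0/3 or 1/6 patients with a DLT. With true DLT rate p,

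P(escalate) = (1 − p)³ + 3p(1 − p)² × (1 − p)³.

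For p = 0.10 to 0.90 this gives 0.906, 0.709, 0.494, 0.309, 0.172, 0.082, 0.032, 0.0088 and 0.0010. All nine entries in the section 10.3 table reproduce. They presuppose that every DLT in the window is counted.

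**5. Illustration of incomplete capture.** Let f be the share of DLTs that goes unrecorded. The rule then acts on p(1 − f). At p = 0.30:

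| f (assumed) | Observed rate | P(escalate) |
| --- | --- | --- |
| 0 | 0.300 | 0.343 + 0.151 = 0.494 |
| 20% | 0.240 | 0.439 + 0.183 = 0.622 |
| 44% | 0.168 | 0.576 + 0.201 = 0.777 |
| 60% | 0.120 | 0.681 + 0.190 = 0.871 |

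The 44% and 60% rows use the shares from step 3 and suppose that every late DLT is lost. The 20% row is a milder scenario with no source in the protocol.

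**The case against.** A reader might infer from 9.2 that weeks 7 to 12 are not required to be captured at all. The protocol does not support that. Table 2 schedules AE monitoring, physical examination, hematology and chemistry on D57, D71 and D85. Note 13 makes AE assessment continuous, and sections 4.2 to 4.5 require DLT assessment to week 12 before escalation.

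Nor does 9.2 govern the DLT decision. It concerns reporting, and the sentence before the 6-week rule describes the routine AE data as collected only for documentation. The specific rules in section 4 would ordinarily prevail over a general *should*. Section 6.2.2 also places drug administration at one hospital, so divergent practice between sites is not shown.

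A further inference, that duration-based DLTs arising late could not be adjudicated, also fails. DLTs are by definition related to CP-675,206, and note 13 and section 7.3.1 follow related events to an outcome.

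The illustration has limits too. The onset range is for diarrhea of unstated grade, and applying its late share to all DLTs is an assumption. Section 6.1.4 attributes the AE experience to early phase trials without separating single-dose from repeated-dose schedules. Losing every late DLT, despite three later scheduled visits and a week-12 review, is an extreme case.

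All of this narrows the consequence. None of it makes the 6-week sentence consistent with the rest of the protocol.

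**Conclusion.** The point holds as an internal contradiction that bears on the primary endpoint. It is not a missing requirement or a flaw in the chosen window: the 12-week choice is stated and justified in 4.2, and 9.2 was not brought into line with it. The practical risk is conditional. It arises only where staff act on 9.2 in preference to Table 2 and section 4, and its direction is then toward under-counting DLTs and toward escalation.

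The size of that risk cannot be read from the protocol. The increases in step 5 show how sensitive the escalation rule is to lost DLTs; they are not estimates of what would happen. With complete 12-week capture, the section 10.3 table stands as printed. The contradiction itself rests on no assumption and should be removed, because it touches the safety data on which each escalation depends.

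**What to change.** Reconcile the last sentence of that paragraph in 9.2 with sections 4.2 and 4.4, Table 2 note 13 and section 7.3.1. AE collection should cover at least the protocol's own 12-week DLT window after CP-675,206 dosing, with unresolved treatment-related events then followed as 7.3.1 already provides. The revised sentence should separate the period for recording new events from the tracking of known ones, so that *followed* no longer carries both meanings. The case report form should use the same period.

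The cost is one sentence, with no new visits or procedures. One detail to settle in the same edit: D85 is 82 days after a D3 dose, two days short of 84. The 3-day visit tolerance in section 7 spans that gap, but the text should say from which day the 12 weeks are counted.

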# 10. DATA ANALYSIS/STATISTICAL CONSIDERATIONS

## **10.1. Trial Populations**

The following population will be assessed: An as-treated population, defined as all patients enrolled in the trial that received radiation therapy and one dose of CP-675,206.

## **10.2. Sample Size Determination**

A minimum of 3 patients will be treated at each dose level prior to escalating to the next dose level, and a minimum of 6 patients will be studied at the MTD to determine its suitability as the recommended dose for Phase 2 combination studies. For details, please refer to Section 4.2, “Dose Escalation Rules”. An estimated maximum of 6 patients will be enrolled at each of 4 dose levels, plus an additional maximum of 6 patients for further evaluation at the MTD (for a total of 30 subjects). Additional patients may be entered as needed at any dose level, including intermediate dose levels. Overall, the sample size is determined empirically and it is expected that approximately 6-32 patients will be enrolled in this trial (allowing for 2 non-evaluable subjects).

## **10.3. Dose Escalation**

The operating characteristics of the dose escalation portion of this trial design are shown in the table below, which provides the probability of escalation to the next higher dose for each underlying true DLT rate. For example, for a DLT that occurs in 10% of patients, there is a greater than 90% probability of escalating. Conversely, for a DLT that occurs with a rate of 70%, the probability of escalating is 3%. (It is assumed that dose escalation occurs with either 0/3 or 1/6 patients with DLT).

| **Probability of Escalating Dose** | | | | | | | | | |  |
| --- | --- | --- | --- | --- | --- | --- | --- | --- | --- | --- |
| True Underlying DLT Rate | 10% | 20% | 30% | 40% | 50% | 60% | 70% | 80% | 90% | |
| Probability of Escalating Dose | 0.91 | 0.71 | 0.49 | 0.31 | 0.17 | 0.08 | 0.03 | 0.009 | 0.001 | |

The probability of failing to observe toxicity (such as DLT) in a sample size of 3 or 6 patients given various true underlying toxicity rates is shown below. For example, with 6 patients, the probability of failing to observe toxicity occurring at least 40% of the time is less than 5%.

| **Probability of Failing to Observe Toxicity** | | | | | | | | | |  |
| --- | --- | --- | --- | --- | --- | --- | --- | --- | --- | --- |
| True Underlying Toxicity Rate | 10% | 20% | 30% | 40% | 50% | 60% | 70% | 80% | 90% | |
| Probability Failing to Observe Toxicity, N=3 | 0.73 | 0.51 | 0.34 | 0.22 | 0.13 | 0.064 | 0.027 | 0.008 | 0.001 | |
| Probability Failing to Observe Toxicity, N=6 | 0.53 | 0.26 | 0.12 | 0.047 | 0.016 | 0.004 | <0.001 | <0.001 | <0.001 | |

##

## **10.4. Analysis of Primary Endpoint**

### **10.4.1. Safety Analysis**

Overall safety profile and toleration of CP-675,206 and irradiation will be characterized by type, frequency, severity (as graded by version 3.0 of the NCI CTCAE), timing and relationship of adverse events to investigational therapy and laboratory abnormalities.

## **10.5. Analysis of Secondary Endpoints**

### **10.5.1. Efficacy Analyses**

#### 10.5.1.1. Best Overall Response

For patients with measurable disease, best overall response will be defined according to the Response Evaluation Criteria in Solid Tumor (RECIST) guidelines. For patients without measurable disease, best overall response can be a CR (no evidence of disease), PR (eg unequivocal progression in non-measurable lesions or new lesion), or SD in all other cases. Listing of patients with their measurability status at baseline and best overall response on study will be provided.

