### **8.2.2. “Target” and “Non-Target” Lesions**

Baseline tumor measurements must be performed not more than 4 weeks (28 days) prior to the initiation of treatment with CP-675,206. Patients must have at least one measurable lesion outside of the radiation field at baseline to be included in the analysis of this endpoint. If the measurable disease is restricted to a solitary lesion, its neoplastic nature could be confirmed by cytology/histology if necessary.

Baseline documentation of tumor sites may include imaging assessment of disease in the chest, abdomen and pelvis. A baseline imaging study of the brain is required.

Target Lesions

• Up to 10 total lesions, a maximum of 5 lesions per organ, that are representative of all involved organs may be selected and recorded as target lesions at baseline. Target lesions should be selected on the basis of their size (lesions with the longest diameter) and their suitability for accurate repetitive measurements (either by imaging techniques or clinically). A non-measurable lesion cannot be selected as a target. A sum of the longest diameter (LD) for *all target lesions* will be calculated and reported as the baseline sum LD. The baseline sum LD will be used as reference to further characterize the objective tumor response of the disease.

Non-Target Lesions

• All other lesions (or sites of disease) should be identified as non-target lesions and recorded as non-target lesions at baseline. Measurement of non-target lesions at baseline is not required and should be recorded as “present.” Each non-target lesion should be documented as either present, absent or new in each subsequent evaluation.

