### **8.2.4. Objective Response Classifications**

The following RECIST criteria will be the primary method utilized in this trial for the assessment and reporting of tumor response data:

- Complete Response (CR): Disappearance of all target and non-target lesions. CR must be confirmed by repeat assessments performed no less than 4 weeks after the criteria for response are first met to qualify as CR;
- Partial Response (PR): At least a 30% decrease in the sum of the longest diameter (LD) of target lesions taking as reference the baseline sum LD. Non-target lesions may persist provided there is no unequivocal progression in these lesions.
- PR must be confirmed by repeat assessments performed no less than 4 weeks after the criteria for response are first met to qualify as PR;
- Progressive Disease (PD): At least a 20% increase in the sum LD of the target lesions from the smallest sum LD recorded since the beginning of therapy or the appearance of one or more new lesions or unequivocal progression of existing non-target lesions; and
- Stable Disease (SD): Measurements demonstrating neither sufficient shrinkage to qualify for PR nor sufficient increase to qualify as PD after the start of treatment taking as reference the smallest sum LD since the treatment started. During this time, non-target lesions may persist provided there is no unequivocal progression in these lesions.

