### **8.2.6. Evaluation of Overall Response**

The best overall response is the best response recorded since the start of treatment until disease progression or recurrence (taking as reference for PD the smallest measurement since treatment started). For CR and PR the best response assignment will depend on the achievement of both the initial establishment and confirmation of CR or PR.

To be assigned a status of Partial Response (PR) or Complete Response (CR), changes in tumor measurements must be confirmed by repeat assessments that should be performed no less than 4 weeks after the criteria for response are first met, per RECIST.If a patient does not achieve a PR or CR but maintains Stable Disease (SD) for at least 10 weeks or more, then the best overall response for the patient will be SD.

| Overall Response | | | |
| --- | --- | --- | --- |
| Target Lesions | Nontarget lesions | New Lesions | Overall response |
| CR a | CR | No | CR |
| CR | Non-CR/Non-PD | No | PR |
| PR b | Non-PD | No | PR |
| SD c | Non-PD | No | SD |
| PD d | Any | Yes or No | PD |
| Any | PD | Yes or No | PD |
| Any | Any | Yes | PD |
| a, Complete Response  b, Partial Response  c, Stable Disease  d, Progressive Disease | | | |

##

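### Section 10.5.1.1 labels progression as PR for patients without measurable disease and gives them no PD category, against the protocol's own response definitions

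*Protocol*

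**What the plan says.** Protocol Section 10.5.1.1 has two rules for best overall response. Patients with measurable disease are classified by RECIST. For patients without it, "best overall response can be a CR (no evidence of disease), PR (eg unequivocal progression in non-measurable lesions or new lesion", with SD for all remaining cases. The section then plans a patient listing that shows baseline measurability next to best overall response.

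The response definitions come earlier in the protocol. Section 8.2.4 includes in progressive disease "the appearance of one or more new lesions or unequivocal progression of existing non-target lesions". Its condition for PR is the opposite: "Non-target lesions may persist provided there is no unequivocal progression in these lesions".

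On who is analysed, Section 8.2.2 says "Patients must have at least one measurable lesion outside of the radiation field at baseline to be included in the analysis of this endpoint". Section 8.2 sets the same condition for being evaluable for response.

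**The concern.** The rule in Section 10.5.1.1 offers only CR, PR and SD. Its example of PR is a growing non-measurable lesion or a new lesion, and PD is missing. A patient in this group who progresses therefore cannot be recorded as having progressed.

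Such patients can be enrolled. The inclusion criteria in Section 5.1 do not ask for measurable disease, and Section 8.2.1 treats bone lesions, among others, as non-measurable.

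What is at stake is the reporting of the secondary efficacy objective. The label goes into a listing that the protocol commits to produce. PR is also what starts the duration of objective response in Section 10.5.1.2, and clinical response is one of the variables in the exploratory immune correlations of Section 10.5.2.1.

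**Working it through.** The protocol states no response rate, power or sample-size figure that depends on this rule, so there is nothing to reproduce. The check is a comparison of texts, followed by a bound on the size.

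**1. The same finding under each section.** Take a patient with only non-measurable disease whose week-8 scan shows a new lesion or unequivocal growth.
- Section 10.5.1.1: PR.
- Section 8.2.4: PD. PR is ruled out by the condition on non-target lesions.
- Section 8.2.6 table, non-target progression: "Any | PD | Yes or No | PD". A separate row codes any new lesion as PD, whatever the other findings.

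**2. Whether PR could be meant.** The table has two rows that lead to PR. One needs target-lesion CR with residual non-target disease. The other reads "PR b | Non-PD | No | PR". Both require a target-lesion response and no new lesion. Section 8.2.2 does not allow a non-measurable lesion to be a target, so a patient with no measurable lesion has no route to PR in the table. The categories that make sense for this group are CR, PD and neither of the two. Section 10.5.1.1 has exactly that shape once PR is read as PD.

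**3. Whether the confirmation rule repairs it.** Section 8.2.6 says "For CR and PR the best response assignment will depend on the achievement of both the initial establishment and confirmation of CR or PR". That is a further hurdle for the PR label, but it does not restore PD. If the label fails for want of confirmation, the patient falls into the residual category of Section 10.5.1.1, which is SD. No path through that sentence ends in PD.

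**4. Consequence for the time variables, read literally.** Let *t* be the date of the scan.
- Section 10.5.1.2 starts the duration of objective response when PR is first documented, which is *t*, and ends it at progression, which is also *t*. Duration = *t* − *t* = 0.
- Section 10.5.1.3 counts the first documented progression as the PFS event, also at *t*.

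One date is then both the start of a response and a progression event.

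**5. Size.** The number of affected patients is not given; it could be anything from none to all of those enrolled.
- In the response-evaluable set of Sections 8.2 and 8.2.2, these patients are excluded, so the shift is 0.
- If they were counted all the same, each would add 1/n to a response proportion. The values of n come from Section 10.2: cohorts of up to 6, and 4 × 6 + 6 = 30 patients, or 30 + 2 = 32 with the allowance for non-evaluable subjects.

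| n | Shift per mislabelled patient |
| --- | --- |
| 6 | 1/6 = 16.7 percentage points |
| 30 | 1/30 = 3.3 percentage points |
| 32 | 1/32 = 3.1 percentage points |

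**The case against.** The best defence is that this is a typing slip which other rules contain. The parenthesis plainly describes progression, PD is the one category missing, and Sections 8.2.4 and 8.2.6 are clear. Section 8.2.6 also counts best response only up to progression and requires PR to be confirmed, while Sections 8.2 and 8.2.2 keep these patients out of the response analysis. The protocol specifies no response-rate estimate, test or threshold. The listing shows measurability beside each response, so a wrong label could be spotted, and a response lasting zero days would expose itself. PFS uses progression directly and is unaffected.

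Most of this stands, and it limits the consequence. It does not make the sentence right: the error is in the current efficacy-analysis text, nothing else in the protocol corrects it, and the listing is a planned output.

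Two stronger readings are tempting but not supported:
- A reader might infer that treatment failures become objective responders and inflate the response rate substantially. That needs the affected patients to be in the denominator, which Sections 8.2 and 8.2.2 rule out, and it needs their number and progression rate, which the protocol does not give. The remark in Section 2.1.1 that bone is the most frequent site of radiation in the metastatic setting does not help: it describes the irradiated lesion and says nothing about whether the patient has measurable disease elsewhere.
- A reader might infer that giving these patients a best response at all contradicts Section 8.2.2. Listing every patient is compatible with analysing a subset. Since Section 10.1 names only an as-treated population, however, a clarifying sentence is worth adding.

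**Conclusion.** The point holds as an error in a classification rule. Section 10.5.1.1 labels progression as PR and omits PD for patients without measurable disease, in conflict with Sections 8.2.4 and 8.2.6. PR is very probably meant to be PD.

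The certain effect of literal use is a wrong label in the best-overall-response listing for any such patient who progresses, together with the contradictory dates shown above. The effect on the response-evaluable set is zero, provided Sections 8.2 and 8.2.2 govern. The per-patient shifts in the table apply only if that restriction is ignored. No total inflation can be stated, because the protocol gives no count of patients without measurable disease.

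The endpoint is secondary. The toxicity endpoint, DLT assessment, dose escalation and MTD do not use response and are unaffected.

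**What to change.** In Section 10.5.1.1, replace PR with PD in the sentence on patients without measurable disease, so that the categories are:
- CR: no evidence of disease;
- PD: unequivocal progression of non-measurable lesions, or a new lesion;
- SD (that is, non-CR/non-PD): all other cases.

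Add one sentence stating that patients without measurable disease outside the radiation field are listed separately and are not counted in the objective-response or duration-of-response summaries, in line with Sections 8.2 and 8.2.2. This wording also settles the status of a patient whose only measurable lesion is the irradiated one.

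The cost is a short wording amendment. No patients, visits or procedures change.
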